### Background and rationale

1.1

Head and neck cancer arises from the epithelial lining of the upper aerodigestive tract and represents the seventh most common malignancy worldwide (1). Radiotherapy, either alone or in combination with concurrent chemotherapy, remains a cornerstone in the management of these malignancies (2). However, these treatment strategies are commonly associated with wide range of oral complications, including oral mucositis, secondary infections, xerostomia, dysgeusia, pain and an increased risk of dental and periodontal diseases. These complications impair essential activities like eating, swallowing, speaking and thereby reducing quality of life of patients. In severe cases, they may lead to treatment interruptions, infections and compromised oncological outcomes (3, 4).

Among the complications, oral mucositis (OM) is one of the most dose limiting toxicity of cancer treatment and it is featured by inflammation and ulceration of oral mucosa, typically developing 5–7 days after the initiation of chemo and radiotherapy. Approximately 40% of head and neck cancer patients receiving chemotherapy alone develop OM, whereas 90%–100% patients receiving concurrent chemo-radiotherapy (5). Evidence from Indian clinical settings indicated that radiation-induced oral mucositis (RIOM) usually appears after a cumulative radiation dose of approximately 20Gy, becomes more widespread at around 30Gy, and reaches peak severity with Grade 3 reactions at cumulative doses of 66 – 70Gy (6).

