#### Criteria for discontinuing or modifying allocated interventions

2.3.3

Participants may be withdrawn from the study prior to completion if they withdraw informed consent at any time without providing a reason, develop serious or intolerable adverse reactions, or experience worsening of RIOM or the emergence of other medical conditions requiring treatment that is incompatible with continued study participation. Participants may also be withdrawn in cases of repeated non-adherence to study procedures, scheduled visits, or the medication regimen, defined as less than 70% drug compliance despite counselling, or if they are unable to be contacted for scheduled assessments despite reasonable efforts.

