### Outcomes

2.5

The primary outcome of the study is the severity of RIOM, assessed using RTOG grading scale. This will be measured as the proportion of participants who develop severe oral mucositis (RTOG grade ≥ 3) at any time during radiotherapy and up to six weeks following completion of radiotherapy, compared between the two study arms. The primary outcome will be assessed from randomisation until the last day of study medication use.

The secondary outcomes include oral mucositis severity assessed using WHO oral mucositis scale, measured as the proportionate reduction in the occurrence and severity of mucositis during radiotherapy and up to six weeks post-radiotherapy. Oral cavity pain, evaluated using VAS as the proportion of participants achieving a minimum two-point reduction in pain intensity and analgesic usage, assessed as the percentage of participants requiring analgesics categorised according to WHO three-step analgesic ladder. Safety outcomes will be evaluated by documenting the number of adverse events reported in each study group. Treatment interruption will be assessed as the proportion of participants experiencing one or more radiotherapy interruptions due to severe RIOM and the total number of days of missed radiotherapy. In addition, body weight changes during radiotherapy, requirement for nasogastric tube feeding, and interruptions in oral intake will be documented as exploratory indicators of nutritional impact. All secondary outcomes, except treatment interruption, will be assessed from randomisation until the last day of study medication use, while treatment interruption will be evaluated until the completion of radiotherapy.

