### Data management

4.3

All study-specific data will be recorded in standardised CRFs. Source documents, including medical records and laboratory reports, will be maintained to allow verification of recorded data. Investigators will document all required participant information in the CRFs, with appropriate justification for any missing data. Data recorded in the CRFs will be routinely cross-verified against source documents, and any discrepancies will be addressed and resolved through data clarification. Treatment details, follow-up information, and scheduled visit dates during post-RT period will be documented in a patient diary. Protocol deviations and the use of concomitant or rescue medications, if any, will also be recorded in the CRFs and reviewed by the investigators at each visit.

Participants who discontinue or deviate from the intervention protocol will continue to be followed, and their data will be included in the final analysis in accordance with the *intention-to-treat* principle. To support participant retention and ensure complete follow-up, regular telephonic communication will be maintained.

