Efficacy analysis will follow a modified *intention-to-treat* approach, including all randomised participants who have undergone at least one post-baseline assessment. Safety analysis will be performed using the per-protocol population. A two-sided *p* value of ≤0.05 will be considered statistically significant. All statistical analyses will be carried out by a statistician using the Statistical Package for the Social Sciences (SPSS) software.

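### The efficacy set needs only one post-baseline visit, which departs from the intention-to-treat commitment in Section 4.3 and suits an ever-grade-≥3 endpoint poorly

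*Protocol article*

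**What the plan says.** All references are to the protocol article.

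- **Section 4.5 (Statistical methods):** efficacy is analysed by modified intention-to-treat, "including all randomised participants who have undergone at least one post-baseline assessment". The proportions are compared by chi-square or Fisher's exact test.
- **Section 4.3 (Data management):** "Participants who discontinue or deviate from the intervention protocol will continue to be followed, and their data will be included in the final analysis", under the intention-to-treat principle. Section 5.2.1 likewise encourages continued follow-up when the intervention is modified or stopped.
- **Section 2.5 (Outcomes):** the primary outcome is "the proportion of participants who develop severe oral mucositis (RTOG grade ≥ 3) at any time during radiotherapy and up to six weeks" after radiotherapy ends. The same paragraph then says: "The primary outcome will be assessed from randomisation until the last day of study medication use".
- **Section 2.3.3:** participants may be withdrawn from the study if, among other reasons, they "experience worsening of RIOM or the emergence of other medical conditions requiring treatment that is incompatible with continued study participation". Intolerable reactions and drug compliance below 70% are further grounds.
- **Section 1.1 (Background and rationale):** for radiation-induced oral mucositis (RIOM), the text reports from Indian settings that it "usually appears after a cumulative radiation dose of approximately 20Gy, becomes more widespread at around 30Gy, and reaches peak severity with Grade 3 reactions", with that peak placed between 66 and 70 Gy.

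**The concern.** There are two linked problems.

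First, Section 4.5 narrows the population that Section 4.3 commits to. Whether someone attends a post-baseline visit is decided after randomisation, by participants and staff who know the allocation. A set chosen that way no longer has the full protection of randomisation.

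Second, one visit is a weak entry condition for an outcome that accumulates over the whole course and six weeks beyond. A participant seen once in week 1 qualifies, yet has been observed only before severe RIOM would be expected. The chi-square and Fisher tests compare simple proportions and make no allowance for unequal observation time. The sentence in Section 2.5 that closes assessment at the last study medication makes short follow-up more likely, because it puts events after early stopping outside the window. Sections 4.3 and 5.2.1 are written to keep collecting data in exactly those participants.

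At stake is the primary comparison. Arm A carries the extra rinse and topical application, each three times daily with timed gaps (Section 2.4.1), so leaving could plausibly differ by arm.

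**Working it through.** **Inputs.** 55–72 Gy over 4–7 weeks (Section 2.3.1); onset at about 20 Gy and grade 3 peak at 66–70 Gy (Section 1.1); severe RIOM of 43.6% on benzydamine, an assumed 15% relative reduction, 20% dropout, 64 evaluable and 80 recruited per arm (Section 2.7).

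**The plan's own dropout figure.** 64 / (1 − 0.20) = 80 per arm, which reproduces. It allows for 0.20 × 80 = 16 leavers per arm. How the 64 was obtained is a separate matter, and nothing here depends on it.

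**Step 1: dose by the first weekly visit, assuming even delivery.**
- Slowest pairing: 55 / 7 = 7.9 Gy per week. Fastest: 72 / 4 = 18 Gy per week.
- If the higher dose goes with the longer course: 72 / 7 = 10.3 and 55 / 4 = 13.8 Gy per week.
- Time to 20 Gy: 20 / 18 = 1.1 weeks to 20 / 7.9 = 2.5 weeks.
- In a 72 Gy course, 66 Gy comes at 66 / 72 = 92% of the way: 3.7 weeks of a 4-week course, 6.4 weeks of a 7-week course.

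On every pairing the first weekly visit falls below the stated onset dose and far below the grade 3 peak. This argument uses the grade ≥3 definition of Section 2.5. Section 4.5 names grade ≥2 for the primary comparison, a separate discrepancy.

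**Step 2: where Sections 4.3 and 4.5 clash.**

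| Participant | Section 4.3 | Section 4.5 |
|---|---|---|
| Stops or deviates, at least one post-baseline visit | included | included |
| Stops or deviates, no post-baseline visit | included, as far as data exist | excluded |

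The strict conflict is confined to the second row. In the first row the set is the same, and the weakness is how little observation is needed to enter it.

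**Step 3: illustration only.** Assume that leavers go before peak RIOM and are counted event-free, with 80 per arm and a true rate of 43.6% in both arms. Neither the counting rule nor the split of leaving by arm is in the protocol. The observed rate is 0.436 × (1 − fraction leaving). With d the difference between arms, se0 the pooled and se the unpooled standard error, the two-sided rejection probability is

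1 − Φ((1.96·se0 − d)/se) + Φ((−1.96·se0 − d)/se).

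| Leaving, A vs B | Observed, A vs B | d (points) | Rejection |
|---|---|---|---|
| 20% vs 20% | 34.9% vs 34.9% | 0 | 5.0% |
| 20% vs 10% | 34.9% vs 39.2% | 4.4 | 8.8% |
| 30% vs 10% | 30.5% vs 39.2% | 8.7 | 21.1% |

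Under the assumed effect, 0.436 × 0.85 = 0.371, a difference of 6.5 points. Equal 20% leaving on the same rule shrinks it to 0.8 × 6.5 = 5.2 points.

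**The case against.** The strongest reply is that this is mostly a mismatch of labels, and much of that reply stands.

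- **The excluded group is probably small.** Assessment is weekly, participants are in-patients during radiotherapy, and missed visits are pursued by telephone (Section 4.2). For nearly everyone who stops or deviates, Sections 4.3 and 4.5 agree.
- **No event-free rule is stated.** A reader might infer that the plan counts early leavers as free of severe RIOM, since a one-visit set, an ever-reached outcome and a window ending with medication point that way. No passage says so. The classification may be set out in an analysis plan that is not shown, and its absence is not an error.
- **The illustration does not measure modified ITT against ITT.** It measures an assumed counting rule. Moving to all randomised participants under that same rule would not remove the bias. The 20% dropout in Section 2.7 is also undated, and some of it may fall after the peak, during the telephone follow-up.
- **Outcome-related withdrawal is a different group.** Someone withdrawn for worsening RIOM already has mucositis that has probably been graded, possibly at grade ≥3. That person is not the week-1 leaver.
- **Severe RIOM in week 1 is not ruled out.** Section 1.1 also places the usual onset of oral mucositis at 5–7 days. The dose argument shows only that severe RIOM would not yet be expected.

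The reply does not remove the conflict in what the article fixes. One section commits to intention-to-treat, another makes entry depend on a post-randomisation visit, and a third ends observation with medication although two sections promise follow-up beyond it.

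**Conclusion.** The concern holds in a limited form. The efficacy set in Section 4.5 departs from Section 4.3. Its one-visit threshold admits participants observed for about 8–18 Gy, before severe RIOM would be expected on the protocol's own dose figures. The end of assessment in Section 2.5 conflicts with the continued follow-up in Sections 4.3 and 5.2.1.

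The size of any bias cannot be derived from the document. The direct exclusion probably affects few participants. The figures of about 9% and 21% rejection show what could happen if incomplete follow-up were read as event-free and leaving differed by 10 or 20 percentage points between arms. They are not estimates for this trial. With equal leaving and no true effect the error rate stays at 5%. The documents do not support the conclusion that the primary result will be biased, or in which direction. They do support settling the set, the window and the status of incomplete follow-up before outcome data are analysed, since enrolment has begun.

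**What to change.** 1. In Section 4.5, make the primary efficacy analysis all randomised participants in their assigned arm, as Section 4.3 already says.
2. Reconcile Section 2.5 with Sections 4.3 and 5.2.1, so that the primary outcome is graded through six weeks after radiotherapy whether or not study medication has stopped.
3. Treat a participant with no grade ≥3 event whose grading stops before the end of that window as missing, not event-free. Multiple imputation using arm, treatment modality and last grade is one suitable method.
4. Exempt participants whose assessments end at documented recovery, as Sections 2.4.1 and 2.4.2 allow. Require that mucositis was recorded first; otherwise someone leaving in week 1 at grade 0 would pass as recovered. Define completeness against the RTOG gradings scheduled in Table 2, which shows none between W8 and W13.
5. Keep the modified ITT set as a sensitivity analysis, and add one that counts early leavers as events.

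**Cost:** changes of wording, a little more analysis and slightly wider intervals. Follow-up after stopping is already promised and dropout is already allowed for in the recruited number.

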### Objectives

1.3

The primary objective of this study is to evaluate the proportionate reduction in the occurrence of severe RIOM, as assessed using RTOG grading scale, among participants receiving a Siddha regimen as an adjunct to standard care compared with those receiving standard care alone, assessed during radiotherapy and at six weeks post-radiotherapy.

The secondary objectives are to assess the proportionate reduction in the severity of radiation-induced oral mucositis using WHO oral mucositis scale at the same time points; to compare oral cavity pain intensity between the study groups using VAS, assessed weekly throughout the study period; to evaluate changes in analgesic usage, including escalation or de-escalation according to the WHO Three-Step Analgesic Ladder, on a weekly basis during the study period; to estimate and compare the proportion of adverse reactions between the study groups; and to evaluate differences in the frequency and duration of treatment interruptions attributable to oral mucositis between the study groups.

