### Adverse event reporting and harms

5.2

Any adverse event occurring after the signing of the informed consent but prior to initiation of the study intervention will be recorded and reported as not related to the study drug. All adverse events occurring from study enrolment until trial completion will be documented and graded using the National Cancer Institute Common Terminology Criteria for Adverse Events (CTCAE), Version 5.0. Any adverse event meeting the criteria for a serious adverse event (SAE) during this period will be reported to the institutional ethics committee (IEC) in accordance with applicable guidelines. Serious adverse events occurring after participant discontinuation will not be reported unless, in the opinion of the investigator, the event is considered possibly related to the study intervention or a study-related procedure. The relationship of adverse events to the study drug will be assessed by the investigators based on temporal association with drug administration and whether the event is unexpected or unexplained in the context of the participant's clinical course, pre-existing medical conditions, and concomitant medications. TPC, when used as an internal medicine, has been associated with suspected adverse drug reactions such as nausea, vomiting, and loose stools, as reported in pharmacovigilance databases. However, no adverse drug reaction reports have been identified for its use as a mouthwash. Based on its safety profile with internal administration, the expected adverse effects in this study may include mild gastrointestinal symptoms such as nausea and vomiting.

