#### Interventions - modifications

5.2.1

Participants who develop adverse reactions that are considered intolerable to the Siddha medicines will have the study intervention discontinued, and the event will be recorded as an adverse reaction. In rare instances of suspected allergic reactions, including skin manifestations, the trial medication will be immediately withdrawn, and the event will be documented as an adverse event. If any biochemical abnormalities are detected during routine laboratory investigations, the study medication will be temporarily withheld until the laboratory values return to normal or clinically acceptable limits. Once the parameters stabilise, the intervention may be restarted at half of the earlier dose, based on the investigator's clinical judgment. In cases where the biochemical abnormalities reappear, the study medication will be permanently discontinued and documented as an adverse event. Even if the assigned intervention is modified or stopped, participants will be encouraged to continue follow-up with the study team so that outcome assessments and relevant study data can still be collected, thereby reducing the possibility of missing data.

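### Safety is assigned to an undefined per-protocol population, which in its usual meaning leaves out participants who stopped because of a reaction and conflicts with the promise to analyse those who discontinue

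*Protocol article*

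**What the plan says.** Section 4.5 (Statistical methods) names two analysis populations. Efficacy uses a modified intention-to-treat set, "including all randomised participants who have undergone at least one post-baseline assessment". For safety it says: "Safety analysis will be performed using the per-protocol population". The article does not define per-protocol.

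The rules for leaving treatment are in two places:
- Section 2.3.3 lists reasons for which a participant may be withdrawn. They include those who "develop serious or intolerable adverse reactions", worsening mucositis, and drug compliance below 70% despite counselling.
- Section 5.2.1 is firmer: "Participants who develop adverse reactions that are considered intolerable to the Siddha medicines will have the study intervention discontinued". For suspected allergy, "the trial medication will be immediately withdrawn, and the event will be documented as an adverse event". A laboratory abnormality that returns after restart leads to permanent discontinuation.

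Section 4.3 (Data management) says that participants who discontinue or deviate are still followed and enter the final analysis under intention-to-treat. Section 5.2.1 also encourages follow-up after the intervention stops.

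Section 5.2 says "All adverse events occurring from study enrolment until trial completion will be documented and graded", and a little later "Serious adverse events occurring after participant discontinuation will not be reported unless, in the opinion of the investigator" the event is possibly related to the intervention or a study procedure. The safety objective in section 1.3 is "to estimate and compare the proportion of adverse reactions between the study groups".

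**The concern.** A safety analysis should cover everyone exposed, because stopping treatment is often the result of harm. Here the broader population is given to efficacy and the narrower one to safety. If per-protocol has its usual meaning (adequate adherence to the allocated regimen without major deviation), a participant who stops for an intolerable or allergic reaction is recorded in the case record form but is absent from the comparison of harms.

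At stake is the safety objective in section 1.3. The Conclusion (section 8) also makes the regimen's prospective value conditional on benefit without added toxicity. A set that omits those who could not tolerate the regimen gives weak support for any such finding.

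**Working it through.** The article states no safety rate, so there is no figure to reproduce. The check has two parts.

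**1. The sections side by side**

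| Event | What happens to treatment | Retained in a per-protocol set, usual meaning? | Retained under section 4.3? |
|---|---|---|---|
| Intolerable reaction to the Siddha medicines | Discontinued (5.2.1) | Usually no | Yes |
| Suspected allergy | Withdrawn at once (5.2.1) | Usually no | Yes |
| Recurrent laboratory abnormality | Permanently discontinued (5.2.1) | Usually no | Yes |
| Serious or intolerable reaction, either arm | May be withdrawn from the study (2.3.3) | Usually no, if withdrawn | Yes, if the participant counts as having discontinued |
| Compliance below 70% | May be withdrawn from the study (2.3.3) | Usually no | Yes, as a deviation |

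The third column rests on the ordinary meaning of the term, because the article gives no definition. The last two columns cannot both govern the safety analysis.

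**2. Size of the understatement in Arm A (illustration)**

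Inputs:
- n = 80 in Arm A (section 2.7: 64 / (1 − 0.20) = 80, which agrees with the stated number).
- s = participants who stop for a reaction. This is assumed and varied over 4, 8, 12 and 16. The top value equals the whole planned dropout, 80 × 0.20 = 16.
- m = 8 other participants with a reaction that they tolerate and who stay on treatment (assumed).

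Formulas:
- All-treated rate = (s + m) / n
- Per-protocol rate = m / (n − s)

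| s | All treated | Per-protocol |
|---|---|---|
| 4 | 12/80 = 15.0% | 8/76 = 10.5% |
| 8 | 16/80 = 20.0% | 8/72 = 11.1% |
| 12 | 20/80 = 25.0% | 8/68 = 11.8% |
| 16 | 24/80 = 30.0% | 8/64 = 12.5% |

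The direction within the arm does not depend on the values chosen. The inequality m/(n − s) < (s + m)/n rearranges to 0 < s(n − s − m). It therefore holds whenever anyone stops for a reaction and at least one remaining participant is free of reactions.

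Reactions that lead to stopping make up 5% to 20% of all treated participants in these cases (4/80 to 16/80). They are absent from the per-protocol set by definition.

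**The case against.** Several counter-arguments have force.

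- **Exclusion is inferred.** Per-protocol is undefined, and section 2.3.3 says only that participants may be withdrawn. This stands as a limit on certainty. It does not rescue the sentence: no ordinary reading of the term reliably keeps everyone who stopped, and section 5.2.1 stops treatment outright for intolerable or allergic reactions.
- **The direction between arms is not proven.** A reader might conclude that the choice must make the Siddha regimen look safer than standard care. The documents do not establish that. The withdrawal criteria in section 2.3.3 apply to both arms, and the number who will stop in each is unknown. What can be said is that the intolerance rule in section 5.2.1 concerns the Siddha medicines, so understatement in Arm A is the more likely result.
- **The harms table would not be empty.** A reader might infer that the per-protocol set shows no reactions at all. Tolerated events remain in it; the definitional zero applies only to reactions that lead to stopping.
- **Serious adverse events after discontinuation.** One could read section 5.2 as letting these go unrecorded. The limiting sentence follows one about the ethics committee, so it can be read as restricting what is reported there and not what is documented. The two statements still need to be reconciled, but loss of data is not shown.
- **Adverse reactions as a measure.** A reader might think that this measure can be positive only in Arm A. Both arms receive benzydamine, and section 7 notes burning and altered taste with current supportive care, so reactions can occur and be compared in both.
- **Safety is secondary and the events are recorded.** True. The primary analysis is unaffected and the set can be corrected before analysis. The sentence nevertheless fixes a poor choice; it is not a detail left open for an analysis plan.

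**Conclusion.** The point holds as a fault in the analysis population. Section 4.5 fixes an undefined per-protocol set for safety. In its usual meaning that set omits participants who stopped because of a reaction, and it is at odds with section 4.3. If 4 to 16 of 80 in Arm A stopped for reactions and 8 others had tolerated ones, the any-reaction rate would be understated by 4.5 percentage points (15.0 − 10.5) to 17.5 percentage points (30.0 − 12.5). These counts are assumptions, since the documents give no expected reaction or stopping rate, and section 5.2 itself expects mild effects. The conclusion rests on the usual meaning of per-protocol. It does not extend to data capture, because sections 5.2 and 5.2.1 still record the events.

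**What to change.** 1. In section 4.5, replace the safety sentence. Define the safety set as all randomised participants who used at least one dose of any study treatment (Siddha regimen or standard of care), analysed by treatment received. A per-protocol safety table should be supplementary at most, with the set defined.
2. For the between-arm comparison, use the proportion of participants with at least one adverse event of any cause, and the proportion with at least one of CTCAE grade 3 or higher.
3. In section 5.2, state that the limit on serious adverse events after discontinuation does not remove them from the documented and analysed data, so that it agrees with the statement that all adverse events to trial completion are documented.

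The cost is a protocol amendment of a few sentences, with matching wording in any analysis plan. On the article's own account, adverse events are already documented from enrolment to trial completion, so no new data collection is needed. Enrolment has begun, so item 3 should be settled promptly, to make sure that sites do not read the limit as a limit on recording.
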